### Outcomes {12}

The primary outcome will be change in mobility status at the conclusion of the intervention (hospital discharge or the 10th day of the intervention, whichever comes first) compared to the baseline assessment. Mobility status will be assessed at both time points using the Short Physical Performance Battery (SPPB), [42–44] a mobility performance assessment that can be administered in <10 min. It tests gait speed, repeated chair stands, and tandem balance, providing a gross assessment of functional balance, speed, and lower extremity power. It is safe and reliable for use with hospitalized older adults [45] and appropriately sensitive to mobility differences in that population [45, 46]. Further, the SPPB has demonstrated the ability to predict adverse health outcomes including in-hospital falls, [47] post-acute facility placement, [42] subsequent disability, [48] multi-morbidity, [42, 43, 49] and all-cause mortality [42, 50].

We will collect secondary outcomes at the time of hospital discharge including discharge disposition, length of stay, and the presence of hospital-acquired complications (falls, venous thromboembolism, pressure ulcers, and hospital-acquired pneumonia). Additional secondary outcomes will be assessed after hospital discharge and compared to baseline measurement of the same assessments: FRAIL scale score, [51, 52] the patient’s self-rated mobility status according to the AM-PAC mobility outpatient short form (compared to baseline AM-PAC 6-Clicks mobility scores using the AM-PAC T-scale), [53, 54] and the patient’s self-rated participation in activities of daily living using both the Index in Activities of Daily Living (Katz ADL) [55] and the Lawton Instrumental Activities of Daily Living Scale [56]. At this post-hospital time point, we will also assess 30-day hospital readmission and scores on the Patient Reported Outcomes Measurement Information System (PROMIS) physical function subscale [57, 58].

As both a secondary outcome and a method for characterizing the in-hospital mobility of both groups, we will use a medical grade accelerometer to measure steps taken, energy expenditure, activity bouts, sedentary bouts, body position, sleep latency, total sleep time, wake after sleep onset, and sleep efficiency. A random subset of 10–20% of patients discharged to home will continue to wear the device for an additional 10 days so that we can assess changes in activity immediately after discharge.

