## Assignment of interventions: allocation

### Sequence generation {16a}

Randomization will be done using a computerized system. A block randomization scheme with a size of 4 will be used to ensure approximately equal numbers of patients per group. Allocation will be stratified within units within hospitals.

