## Statistical methods

### Statistical methods for primary and secondary outcomes {20a}

#### Statistical analyses

The main analysis will follow the intention-to-treat principle. The primary outcome, change in the SPPB from baseline to discharge (or 10 days), will be compared between the groups using an independent samples *t*-test. The large sample size should ensure that any confounding variables are equally distributed between groups. However, if we identify that any baseline variables are unbalanced and also associated with the outcome, we will model SPPB using a linear mixed-effects model to control for potential confounding. The fixed effects will include group, measurement time point, their interaction, site, and any unbalanced baseline variables. Secondary binary outcomes (discharge disposition and hospital-acquired complications) will be assessed using the chi-square test. The secondary longitudinal outcome (mobility improvement 30 days after hospital discharge) will be modeled using linear mixed-effects models.

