Many potential limitations for our study are mitigated by the study’s design. For example, patients who are enrolled may be unable or unwilling to ambulate three times each day. If adherence is lower than expected in interim analyses, we will compare adherence rates across sites and attempt to identify and spread best practices. If that is not successful, we would still likely have sufficient power to detect a difference in our primary (>99% power with 70% adherence) and secondary outcomes (80% power with 70% adherence). Depending on the ease of enrollment, we may decide to enroll additional patients with the same resources. We anticipate heterogeneous patients, sites, and controls. Given our large sample, we anticipate that all of these important covariates will be balanced between the intervention and control arms. If we find that they are not, we will adjust our outcomes for important confounders. If we are unable to directly identify subgroups for whom the intervention is most beneficial, we will create a score, based on logistic regression, to identify patients who benefit if they score above a certain threshold. Alternatively, we will provide recommendations and tools to enable individual hospitals to incorporate our prediction model into the electronic health record and identify patients directly from the model.

While functional decline in the hospital is multifactorial, general out-of-bed mobility is a modifiable factor for many patients. This randomized controlled trial will test the effectiveness of MT-assisted ambulation on outcomes that matter to both patients and hospitals, including functional status, hospital discharge disposition, and the incidence of potentially avoidable hospital complications. It will also provide a useful estimation of cost implications to help hospital administrators assess the feasibility and utility of creating MT positions in their own hospitals.

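### The fallback mixed model enters unbalanced baseline variables only as main effects, so its group-by-time estimate of the effect on SPPB change is left essentially unadjusted

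*Protocol article*

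**What the plan says.** Outcomes {12} defines the endpoint as a change: "The primary outcome will be change in mobility status at the conclusion of the intervention", compared with baseline, with SPPB measured at both time points. The Statistical analyses section agrees: "The primary outcome, change in the SPPB from baseline to discharge (or 10 days), will be compared between the groups" by an independent-samples t-test.

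The same section then gives a fallback. It applies "if we identify that any baseline variables are unbalanced and also associated with the outcome", and in that case "we will model SPPB using a linear mixed-effects model to control for potential confounding". The terms are listed: "The fixed effects will include group, measurement time point, their interaction, site, and any unbalanced baseline variables". The Discussion repeats the intention for covariates that turn out not to be balanced: "If we find that they are not, we will adjust our outcomes for important confounders". No section adds a covariate-by-time term or replaces this model with a regression of change, or of final SPPB, on the covariates.

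**The concern.** Because measurement time and group-by-time are in the model, baseline SPPB is one of the two responses. The effect on the primary outcome is then the group-by-time coefficient. A baseline variable confounds a comparison of changes only through its relation to change, which in this model would be a covariate-by-time term. That term is not listed. The model is introduced to remove an imbalance, but the coefficient that answers the primary question cannot respond to it when the data are complete.

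The harm would be false reassurance. The trial could report an adjusted SPPB effect that is numerically the unadjusted one, and readers would take it that chance imbalance had been dealt with.

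**Working it through.** **1. Algebra.** Write the listed model for patient i at visit t (0 = baseline, 1 = discharge or day 10):

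SPPB_it = b0 + b1·group + b2·t + b3·(group × t) + site + b4·X + patient effect + error

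X and site do not change between visits, so

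E[SPPB_i1 − SPPB_i0 | group, X, site] = b2 + b3·group.

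Neither b4·X nor site remains. With both visits observed, the estimate of b3 is the raw difference in mean change, which is the t-test estimate. X can move only b1, the baseline difference between groups.

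**2. Numerical check, complete data.** The protocol gives no figure for this model, so there is none to reproduce.

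- *Simulated trial, no true effect* (1350 per arm, SD of change 2.7, covariate correlated 0.4 with change, imbalance 0.096 SD). Raw difference in change: 0.25418. Planned model: 0.25418. With covariate-by-time and site-by-time terms: 0.15934, identical to regressing change on group, site and X. Entering baseline SPPB itself as the unbalanced main effect also returned 0.25418.
- *Twelve simulated trials of 3000* (imbalance 0.2 SD, slope 1 point of change per SD of X). Mean t-test estimate: 0.6445. Planned model: 0.6445 (largest difference in any trial about 1e-13). With the time interactions: 0.4279. The gap, 0.6445 − 0.4279 = 0.217, is the slope times the realised imbalance.
- *Same trials, X predicting SPPB level but not change.* 0.426 against 0.428, so nothing needed adjusting.

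Each estimate carries sampling error; the gap between planned and corrected model is the quantity of interest.

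**3. With 10% of final scores missing.** Three separate runs, each with its own assumptions:

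| Run | Without covariates | Planned model | With time interactions |
|---|---|---|---|
| 0.2 SD imbalance, slope 1 | 0.644 | 0.648 | 0.437 |
| Covariate correlated with change | 0.385 | 0.356 | 0.205 |
| As the first bullet above | – | 0.252 | 0.156 |

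Exact equality is lost, but most or all of the imbalance stays in the treatment effect.

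**4. Size.** From Sample size {14}: 3000 patients less 10% dropout gives 2700, or 1350 per arm; SD of change 2.7; MCID 0.54; two-sided alpha 0.05. Assumed here, because the documents give no values: correlation r of the covariate with change, and imbalance expressed as a z statistic.

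- Imbalance in SD units = z·√(2/1350) = z × 0.0385, so 0.075 at z = 1.96 and 0.096 at z = 2.5.
- Bias = r × 2.7 × imbalance.
- With no true effect and given that imbalance, the test statistic is N(r·z, 1 − r²), and the conditional false-positive rate is P(|Z| > 1.96).

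| r | Bias, z = 1.96 | Rate, z = 1.96 | Bias, z = 2.5 | Rate, z = 2.5 |
|---|---|---|---|---|
| 0.1 | 0.02 | 5.3% | 0.03 | 5.6% |
| 0.2 | 0.04 | 6.3% | 0.05 | 7.4% |
| 0.3 | 0.06 | 7.9% | 0.08 | 10.5% |
| 0.4 | 0.08 | 10.1% | 0.10 | 14.8% |
| 0.5 | 0.10 | 12.9% | 0.13 | 20.6% |

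The largest bias shown is 0.13/0.54 = 24% of the MCID. Across 5000 simulated trials at r = 0.4 and z = 2.5 the conditional rate was 15.2% for the change comparison and 5.2% with the covariate adjusted on the change. Averaged over randomisations (z drawn from a standard normal), the rate returns to 5%.

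**The case against.** **The contrast to report is not named.** The fallback models SPPB rather than its change, and the Abstract gives the primary outcome as the score at discharge. The model's group difference at discharge (b1 + b3) does respond to the covariates. Simulated with 1350 per arm, 0.096 SD imbalance and no true effect, it went from 0.097 to −0.006 when X predicts level only, from 0.203 to 0.047 when X predicts level and change, and from 0.107 to 0.055 when X predicts change only. A reader might infer that the planned model does nothing at all; that is too strong, and holds only for group-by-time with complete data. But Outcomes {12} and Statistical analyses both define the endpoint as change, so group-by-time is the natural reading.

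**The article is condensed, and its list may not be exhaustive.** A fuller document could add terms. Still, the article is not silent: it specifies one interaction and no other, and an analyst following it would fit this model.

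**The trigger may never fire.** Among some 3000 randomised patients, chance imbalance should be small, the main analysis remains the t-test, and the r and z values above are assumptions. All of this stands and limits the consequence. However, the trigger requires association with the outcome, defined as change, so when it does fire it picks out the variables for which the omission matters.

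**Site.** A reader might also infer that site imbalance is credited to treatment. The documents do not support that as a practical problem: "Allocation will be stratified within units within hospitals", so site is close to balanced by design.

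**Conclusion.** The point holds: the stated fallback does not serve its stated purpose for the primary endpoint. The algebra needs only that the effect on change is read from group-by-time and that both visits are observed. With about 10% of final scores missing, the simulations show the imbalance largely or wholly uncorrected.

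The consequence is modest. Under the assumptions above, the residual bias runs from about 0.02 to 0.13 points.

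Three stronger inferences are not supported:

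- That the trial's type I error is inflated overall. The rates above 5% apply only given the assumed imbalance and correlation.
- That the bias should be judged against 0.35 points as the difference the trial is sized on. Sample size {14} calls 0.35 a smaller difference, puts the MCID at 0.54, and says the sample size was chosen mainly for secondary outcomes.
- That the 30-day longitudinal models share the fault. The protocol lists no baseline adjusters for them.

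The wording should be corrected; the t-test as main analysis is not called into question by this point.

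**What to change.** In Statistical methods for primary and secondary outcomes {20a}, let the fixed effects be group, time, group-by-time, site, each baseline adjustment variable, and each adjustment variable by time, and state that group-by-time is the reported treatment effect.

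The alternative is a regression of SPPB change on group, site and the adjustment variables. Regressing final SPPB on the same terms plus baseline SPPB would also remove the imbalance, though its estimate need not match the change regression exactly. One form should be chosen and named.

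A site-by-time term may be added for consistency but will matter little. The same form should carry over to the 30-day models only if baseline adjusters are used there.

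The cost is one sentence and a few degrees of freedom out of about 2700 patients, with no new data.

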### Sample size {14}

A sample size of 3000 has >99% power to detect a difference in SPPB change as small as 0.54 points (the MCID) between the two groups at a two-sided alpha of 0.05, assuming a common SD of 2.7 for the SPPB change, 20% non-compliance, 10% dropouts, and an interim analysis. The estimates for MCID and SD are based on observation of older acute care medical patients [43, 44]. Using these same assumptions, the power is still 92% for detecting a smaller difference of 0.35. Therefore, we expect ample statistical power for analyzing the primary outcome. The main reason for selecting this sample size is to ensure that the analyses of important secondary outcomes are not underpowered. The most important of these is discharge disposition, because even a small absolute difference in the number of patients discharged to home, as opposed to a skilled nursing facility, is clinically important. We will be able to detect a 7% difference in discharge to home vs. SNF with 98% power.

For other binary secondary outcomes (a combination of venous thromboembolism, pneumonia and falls, 30-day mortality, or 30-day readmission), the study will have 85% power to detect a 33% reduction assuming an 8% rate in the control group. Because these outcomes are not contingent on patient cooperation, we anticipate no dropouts. For secondary continuous outcomes such as length of stay, assuming 20% non-compliance rate, the power to detect a 4-h difference (0.167 days) is 95%.

Regarding the cost analysis, there is no accepted way of doing a power calculation. However, we tried adding $300 (an approximation of the cost of the intervention) to the costs of each of 1500 patients drawn randomly from a sample of 3000 Cleveland Clinic medical inpatients over the age of 65 with an AM-PAC 6-Clicks score between 16 and 20. We then performed a *t*-test on the log-transformed costs, as described in the economic analysis section, and we were able to detect the increase with a p-value of 0.03, indicating that should the intervention increase costs by an amount equal to the cost of the intervention, we should be able to identify it. Similarly, if the intervention decreases total costs by $300 or more (not including the costs of the intervention), we should have sufficient power to detect it.

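### Discharge disposition, the outcome that mainly sets N = 3000, is tested with a plain chi-square that ignores hospital and baseline function: valid, but mildly conservative and less efficient than it need be

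*Protocol article*

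**What the plan says.** - **Test.** Under Statistical analyses {20a}: "Secondary binary outcomes (discharge disposition and hospital-acquired complications) will be assessed using the chi-square test". Site appears in that section only as a fixed effect in the SPPB mixed model, which is itself a fallback used if baseline variables prove unbalanced.
- **Allocation.** Under Sequence generation {16a}: "A block randomization scheme with a size of 4 will be used to ensure approximately equal numbers of patients per group", and "Allocation will be stratified within units within hospitals".
- **Why 3000.** Under Sample size {14}: "The main reason for selecting this sample size is to ensure that the analyses of important secondary outcomes are not underpowered". On those outcomes it adds: "The most important of these is discharge disposition". The power claim is: "We will be able to detect a 7% difference in discharge to home vs. SNF with 98% power". No control rate is given.
- **Baseline data.** Eligibility criteria {10} requires a 6-Clicks score of 16 to 20 at entry. Section {18a} has the SPPB done at baseline. Outcomes {12} lists placement in a post-acute facility among the events that the SPPB has been shown to predict.
- **Adjustment elsewhere.** The Discussion allows adjustment for important confounders if covariates turn out unbalanced. Section {20b} plans a sensitivity analysis of heterogeneity by site. Neither changes the main test for the binary outcomes.

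**The concern.** Blocked allocation within units balances the arms within each hospital, so differences between hospitals in how often patients go home largely drop out of the treatment contrast. A plain 2x2 chi-square still counts those differences in its variance. When the strata predict the outcome, the test is therefore slightly conservative, and an interval built on the same variance is slightly too wide.

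A second, separate loss comes from leaving out baseline SPPB and 6-Clicks. Allocation is not stratified on these, so omitting them does not make the test conservative. It only forgoes precision that adjustment would give.

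At stake is precision on the outcome for which most of the sample is being enrolled. The Discussion expects patients, sites and controls to be heterogeneous, so it is hard to argue that hospital carries no information.

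**Working it through.** **Inputs from the article.** N = 3000, taken as 1500 per arm; a 7-point difference with 98% power (Sample size {14}). Two-sided alpha of 0.05 is stated there for the primary outcome and assumed here for disposition. The 20% non-compliance is stated there for the SPPB and length of stay, not in the disposition sentence.

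**Assumptions, not in the article.** Control home rate of 60%; five equal-sized hospitals; the spread of hospital rates; the variance explained by the covariates.

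**Step 1: the plan's own figure.** With pooled variance under the null and no dilution, power for 7 points is 97.2%, 97.1%, 97.9%, 99.2% and 99.9% at control rates of 40%, 50%, 60%, 70% and 80%. The stated 98% is reproduced near 60%.

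**Step 2: unadjusted power at 60%.** SE = sqrt{[p1(1 - p1) + p2(1 - p2)]/1500}; power = Phi(d/SE - 1.96).
- 60% vs 67%: SE = sqrt[(0.2400 + 0.2211)/1500] = 0.01753; d/SE = 3.99; power 97.9%.
- 60% vs 65.6% (0.8 x 7 = 5.6 points): SE = sqrt[(0.2400 + 0.2257)/1500] = 0.01762; d/SE = 3.18; power 88.8%.

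**Step 3: share of variance between hospitals.** Share = var(hospital rates)/[p(1 - p)].
- Rates 50, 55, 60, 65, 70%: 0.0050/0.24 = 0.021.
- Rates 45, 52.5, 60, 67.5, 75%: 0.01125/0.24 = 0.047.

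**Step 4: effect of accounting for hospital.** Multiply the variance by (1 - share). The true size of the plain test is 2[1 - Phi(1.96/sqrt(1 - share))], and its intervals are too wide by 1/sqrt(1 - share) - 1.

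| Share | Power, 7 points | Power, 5.6 points | True size of plain test | Excess width |
|---|---|---|---|---|
| 0 | 97.9% | 88.8% | 5.0% | 0 |
| 0.021 | 98.1% | 89.5% | 4.8% | 1.1% |
| 0.047 | 98.3% | 90.2% | 4.5% | 2.4% |

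The gain is 0.2 to 0.4 points at 7 points, and 0.6 to 1.4 points at 5.6 points.

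**Step 5: check by simulation.** With 25 assumed units, blocks of 4, a between-unit SD of 10 points and 4000 runs, the plain chi-square and the Cochran-Mantel-Haenszel test had power of 97.8% and 98.1% at 7 points, and 89.0% and 89.8% at 5.6 points. This agrees with step 4.

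**Step 6: adding baseline SPPB and 6-Clicks.** Let R2 be the total variance explained and approximate the adjusted variance by (1 - R2) times the unadjusted one.

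| R2 | Power, 7 points | Power, 5.6 points |
|---|---|---|
| 0.05 | 98.4% | 90.3% |
| 0.10 | 98.8% | 91.8% |
| 0.20 | 99.4% | 94.4% |

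The size formula in step 4 does not apply to the covariate part of R2, because allocation is not balanced on those variables.

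**Step 7: complications.** For the composite at 8% in controls with a 33% reduction, a between-unit SD of 1 to 4 points gives a gain of 0.04 to 0.65 power points.

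**The case against.** The strongest reply is that nothing here is wrong. The chi-square controls type I error and is consistent with the 98% claim. At the effect that the protocol actually states, little power is left to recover. The article gives no interval method for these outcomes, which may sit in an analysis plan that is not shown. All of that stands, and it limits the point to efficiency.

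Three stronger readings are tempting, and the documents do not support them.
- A reader might infer that ignoring the stratification costs the equivalent of several hundred patients. Gains of that order need an R2 of 10% to 20%, which must come mostly from baseline covariates. Nothing in the article says how well SPPB or 6-Clicks predicts going home in this cohort, and restricting entry to five 6-Clicks values suggests the low end of the range.
- A reader might put 10% explained variance into the size formula and conclude that the nominal 5% test really runs at 3.9%. Only variance in factors balanced by the allocation has that effect. The hospital scenarios give 4.5% to 4.8%. Reaching 3.9% from strata alone would take a between-unit SD of about 15 points, for which the article offers no basis.
- A reader might extend the point to the complications with equal force. Step 7 shows that the gain there is negligible.

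It can also be said that the Discussion already provides for adjustment. That provision depends on observed imbalance. Stratification makes imbalance by hospital unlikely, and the precision gained from a prognostic covariate does not depend on imbalance. The site sensitivity analysis leaves the main test as it is. So this part of the reply does not remove the point.

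The gain matters most if adherence is poor. For 70% adherence the Discussion quotes 80% power on secondary outcomes, without naming one. Diluting 7 points to 0.7 x 7 = 4.9 gives 79.2% by the step 2 formula, and 81.2%, 83.3% or 87.3% with R2 of 5%, 10% or 20%.

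**Conclusion.** The point holds as a modest loss of efficiency, mainly for discharge disposition. The planned test is valid and mildly conservative. Hospital strata alone are worth well under 1 power point at the stated 7-point difference and at most about 1.4 points at 5.6 points. Baseline SPPB and 6-Clicks could bring the total gain at 5.6 points to between 1.5 and 5.6 points, but only if the assumed R2 of 5% to 20% is reached.

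These figures rest on an assumed 60% control home rate, the assumed spread between hospitals, and a dilution that the article does not apply to disposition. With the same formula and hospital shares at 5.6 points, a 50% control rate gives 86.8% rising to 87.5-88.3%, and a 70% rate gives 93.2% rising to 93.7-94.3%. The conclusion does not depend on the control rate chosen.

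**What to change.** For discharge disposition, replace the chi-square as the main analysis with one prespecified estimator: logistic regression on treatment, hospital, baseline SPPB and 6-Clicks, standardised to a marginal risk difference with a 95% CI. The minimum alternative is a Mantel-Haenszel risk difference stratified by hospital. Use hospital rather than unit as the stratum, to avoid sparse cells. Keep the chi-square as a descriptive check, and do not make adjustment depend on observed imbalance. For the complications, stratifying by hospital is optional.

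The cost is one sentence in Statistical analyses {20a}, or in the analysis plan if it is not already there. No new data and no change to the sample size are needed. It should be fixed before any comparison of disposition between the arms is seen.
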